#### ABSTRACT

Some authors point low adherence to drug treatment as a public health problem with a variable magnitude of 15% to 93% for patients with chronic diseases, being characterized as an "invisible epidemic". In Brazil, few clinical trials were identified evaluating interventions with primary outcome on non-adherence, with most of the participants being carriers of cardiovascular diseases and none of those with inflammatory bowel diseases (IBD). There is a gap in knowledge production of interventions which may impact the non-adherence of patients with IBD, evaluated through studies with randomized clinical trial design, characterizing this study as innovative. IBD are part of the Clinical Protocols and Therapeutic Guidelines of the Ministry of Health with wide coverage of oral and parenteral drug treatment. For this reason, it is of fundamental importance to evaluate and implement measures with the aim of increasing adherence to the prescribed treatment. The present study has as general objective to evaluate the impact of an intervention program in non-adherence to drug treatment in patients with Ulcerative Colitis (UC). This is a prospective longitudinal experimental study with a pragmatic randomized clinical trial design, scheduled to begin in March 2019. Semi-structured interview technique will be employed using the Brasil SF-36 and the Morisky-Green-Levine test, in addition to questionnaires prepared specifically for this study for data collection and secondary data obtained from participants' records, when necessary. The data will be inserted in a database built with the statistical package SPSS, version 21.0. Participants of the Control Group (CG) will not receive the interventions, while those of the Intervention Group (IG) will receive the intervention program individually in a private setting. The program will consist of educational interventions and behavioral interventions applied for a period of 6 months. Socio-demographic, economic, clinical, pharmacotherapeutic, non-adherence and quality of life variables will be analyzed. It will be considered a bilateral (1-alpha) significance level of 95%, power (1-beta) with 80% probability of detection, sample size ratio between exposed / unexposed of 1, percentage of unexposed positive 50% and percentage of exposed positive 80%, Odds Ratio: 4, risk ratio / prevalence of 1.6 and risk / prevalence difference of 30, calculation generated through OpenEpi, version 3.01, was calculated 45 participants in each group (GC and GI) for RCU patients with a total

sample size of 90. Quantitative variables will be described as means (standard deviation) or medians (interquartile range), while qualitative variables will be described with absolute and percentage frequency measures. To compare the exposed (GI) and non-exposed (CG) groups in relation to the qualitative variables, the chi-square test or Fischer's exact test, when recommended, will be used. The comparison of the quantitative variables between the exposure groups will be performed by applying the Student t test for unpaired samples or, if indicated, the non-parametric Mann-Whitney test. The occurrence (incidence) of the study outcomes (non-adherence) will be calculated by the ratio of the total number of participants non-adhering to the treatment and the total number of participants in the group, multiplied by 100, calculated separately for the intervention and comparison groups. The relative risk (RR) with the respective 95% confidence interval (95% CI) will be used as a measure of effectiveness, obtained by the ratio between the incidence of the intervention group and the incidence of the comparative group. For adjustments for potential confounders, Poisson regression with robust variance will be used to estimate RR adjusted with their respective 95% CI. Associations with p values less than 0.05 will be considered significant.

**Key-words**: medication adherence, randomized controlled trial, ulcerative colitis.

#### INTRODUCTION

Some authors point to low adherence to drug treatment as a public health problem with a magnitude varying from 15 to 93% for patients with chronic diseases, with an estimated average of 50%, depending on the method used, characterized as an "invisible epidemic". The lack of adherence generates direct and indirect costs, in addition to clinical, social and environmental repercussions, and it is therefore important not only to identify its magnitude, but also to plan and implement solutions to effectively address this issue[2].

Faced with this reality, global strategies have been presented as promising in the engagement against non-adherence. In 2007, the Brazilian Ministry of Health published the "Guidelines for the Strengthening of Care Actions for People Living with HIV/AIDS"[3] and in 2016 entitled "Synthesis of Evidence for Health Policies: Adherence to drug treatment of patients with chronic diseases"[4]. These texts present the global panorama of the lack of adhesion and possibilities of confrontation, based on international studies.

Inflammatory bowel diseases are part of the Clinical Protocols and Therapeutic Guidelines of the Ministry of Health [5] with wide coverage of treatment with the provision of oral and parenteral drugs. For this reason, the evaluation and implementation of measures to increase adherence to prescribed treatment is of fundamental importance.

#### AIMS

**GENERAL AIM**

To evaluate the impact of an intervention program on the rate of non-adherence to drug treatment in patients with Ulcerative Colitis (UC).

#### SPECIFIC AIMS

1. To assess possible factors associated with the impact of an intervention program on non-adherence to drug treatment in patients with UC;
2. To evaluate the impact of an intervention program on the quality of life of patients with UC.

#### PROPOSED METHODOLOGY

**Study Location**

The study will be carried out at the Integrated Pharmacy of Medicines in Specialized Care (FIMAE) in partnership with the IBD outpatient clinics of the Roberto Santos General Hospital (HGRS) and the [name] University Hospital of UFBA (HUPES), which are references in Inflammatory Diseases. Intestinal (IBD). FIMAE is a public unit of the Health Department of the State of Bahia (SESAB) responsible for dispensing medication to patients with IBD.

#### Study Design

This is a prospective longitudinal experimental study with a pragmatic randomized clinical trial design, in which attention will be paid to the preservation of routine care and service conditions, to favor the application of the study results to the operational conditions of the service in question. The study is scheduled to start in March 2019 with a duration of 36 months.

#### Target Audience

The target audience will be patients diagnosed with UC in the State of Bahia treated by the Unified Health System (SUS) at FIMAE.

#### Ethical Aspectcs

The study will be submitted to the Research Ethics Committee of the Universidade do Estado da Bahia (CEP/UNEB) through Plataforma Brasil for analysis. After approval of the project by the CEP, the Free and Informed Consent Term (ICF) (Appendix 1) will be presented and signed by the patients before entering the research for a subsequent interview, application of the research instruments, as well as a review of medical records and interventions.

In order to guarantee the safety of the information collected, the computers will be used exclusively for research and will be configured to lock with a password that is restricted to designated researchers. All physical documentation will be kept in its own locker with a restricted access key, also to protect the integrity of the information [6].

#### Inclusion Criteria

Patients diagnosed with UC who, during the capture stage, meet all the criteria listed below will be included in the research: they have at least 3 months of active registration at FIMAE; prescribed with at least 01 (one) drug to treat UC; aged 18 years or over; able to respond to the research instruments; who agree to sign the TCLE; that they are assisted by the IBD outpatient clinics at the HGRS or HUPES; who have a cell phone.

#### Exclusion Criteria

Patients who do not meet the research criteria will be excluded, as well as patients who are classified as adherent during the recruitment stage.

#### Participants’ Allocation

After signing the informed consent, the participants will be submitted to the research protocol (Appendix 2). They will be allocated to an Intervention Group (IG) or Control Group (CG) using a randomization technique using a previously generated list of random numbers, before allocation. Allocation confidentiality will be preserved, as the researchers who will carry out the intervention and measure the outcomes will be different, therefore, those who will carry out the outcome assessment will be “blind” and will not know in which group each participant was allocated.

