#### Sample Calculation

We will consider a bilateral significance level (1-alpha) of 95%, power (1-beta) with 80% probability of detection, sample size ratio between exposed/unexposed of 1, percentage of positive unexposed of 50%[13] and percentage of positive exposure of 80%, Odds Ratio: 4, risk/prevalence ratio of 1.6 and risk/prevalence difference of 30, the calculation generated through OpenEpi, version 3.01, calculated 45 participants in each group (CG and IG) for UC patients, with a sample size of 90.

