#### Statiscal Analysis

Quantitative variables (age, disease duration, UC severity score, for example) will be described as means (standard deviation) or medians (interquartile range), while qualitative variables (gender, marital status, education, for example) will be described with absolute and percentage frequency measures. To compare exposed (GI) and non- exposed (CG) groups in relation to qualitative variables, the chi-square test or Fisher's exact test will be used, when recommended. The comparison of quantitative variables between exposure groups will be performed by applying Student's t test for unpaired samples or, if indicated, the nonparametric Mann-Whitney test.

The occurrence (incidence) of the study outcomes (non-adherence) will be performed by the ratio between the total number of participants who did not adhere to the treatment and the total number of participants in the group, multiplied by 100, calculated separately for the intervention and comparative groups. The relative risk (RR) with the respective 95% confidence interval (95%CI) will be used as a measure of efficacy, obtained by the ratio between the incidence of the intervention group and the incidence of the comparative group. For adjustments for potential confounders, Poisson regression with robust variance will be used to estimate adjusted RR with the respective 95%CI. Associations with p values lower than 0.05 will be considered significant.

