**ADHERENCE DATA: MORISKY-GREEN-LEVINE TEST (MGLT)**

**Instructions**: mark below with an “X” according to the treatment for UC

|  |  | **YES** | **NO** |
| --- | --- | --- | --- |
| **NON INTENTIONAL** | 1. Do you ever forget to talke your medicine? |  |  |
|  | 2. Are you careless at times about taking your medicine? |  |  |
| **INTENTIONAL** | 3. When you feel better do you sometimes stop taking your medicine? |  |  |
|  | 4. Sometimes if you feel worse when you take the medicine, do you stop taking it? |  |  |

1. According to MGLT, classify:
   1. Adherent, if answered NO to ALL questions
   2. Moderate adherence, if answered YES to 1 or 2 questions
   3. Low adherence, if answered YES to 3 or 4 questions

(9) NA

1. Non-adherence tipology according to MGLT: (1) Intentional (2) Non-intentional (3) Both (9) NA

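### The crude relative risk named as the measure of efficacy uses no baseline adherence information, and entry MGLT level is not fixed in the planned adjusted analysis

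*Protocol*

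**What the plan says.** All references are to the protocol.

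- **Exclusion Criteria** removes patients who do not meet the research criteria, "as well as patients who are classified as adherent during the recruitment stage".
- **Appendix 3, MGLT form**, classes four NO answers as adherent. The next class is "Moderate adherence, if answered YES to 1 or 2 questions", and three or four YES is low adherence. Both of these classes are eligible. Appendix 4 repeats the same classes for the final visit.
- **Data Categorization** has the MGLT recorded at Time 0 and at 6 months.
- **Participants' Allocation** assigns patients "using a previously generated list of random numbers, before allocation". It mentions neither strata nor blocks.
- **Statistical Analysis** takes as its measure of efficacy the RR of non-adherence, "obtained by the ratio between the incidence of the intervention group and the incidence of the comparative group". It then plans an adjusted RR from a robust-variance Poisson model, for confounders that it does not name.

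**The concern.** The entry rule makes baseline adherence constant on the yes/no scale used for the outcome: every participant starts non-adherent. Adjusting for baseline on that scale would adjust for nothing. The information survives only in the YES count or in the split between moderate and low adherence, and it is used only if one of these is named.

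If the 6-month outcome uses the same cut as entry, a patient who enters with one YES has one answer to change and a patient with four has four. A baseline reading on the same instrument is a natural candidate for a strong predictor. That is reasoning; the protocol gives no data on it.

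At stake is how precisely the trial of 90 estimates its effect, and how convincing its result is if the groups happen to differ in entry level. If covariates are left open, they could also be chosen after such a difference is seen.

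**Working it through.** **1. The plan's own figure.** Sample Calculation gives "We will consider a bilateral significance level (1-alpha) of 95%, power (1-beta) with 80% probability of detection", "percentage of positive unexposed of 50%[13] and percentage of positive exposure of 80"%, and "sample size ratio between exposed/unexposed of 1". Without continuity correction:

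n = [1.96·√(2·0.65·0.35) + 0.8416·√(0.5·0.5 + 0.8·0.2)]² / 0.30² = (1.322 + 0.539)² / 0.09 = 38.5, so 39.

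With the Fleiss correction:

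n = (38.5/4)·[1 + √(1 + 4/(38.5·0.30))]² = 44.9, so 45.

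The stated 45 per group reproduces, and this point does not change it. Uncorrected power at 45 per group is 86.0%.

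**2. Assumptions.** The protocol gives neither the share of low-adherence entrants nor how far entry level predicts outcome, so both are varied. I read the 50% and 80% as adherence, which makes non-adherence 50% against 20%. I take 6-month non-adherence as any YES answer. Allocation is taken as simple randomisation.

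**3. Size of a chance imbalance.** With 45 per group and low-adherence share p, the SD of the between-group difference in share is √(2p(1−p)/45):

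- p = 0.25: 9.1 points, 95% range ±1.96 × 9.1 = ±17.9
- p = 0.40: 10.3 points, 95% range ±20.2

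A gap of 7 or more patients occurs in about 11% and 16% of trials respectively (simulation).

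Suppose low-adherence entrants have 6-month non-adherence 20 to 40 points higher. The outcome difference then moves by up to 17.9 × 0.20 = 3.6 to 20.2 × 0.40 = 8.1 points at the 95% limits.

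**4. Yardstick.** The SE of the crude difference is √(0.25/45 + 0.16/45) = 9.5 points, a 95% half-width of about 19. The 3.6 to 8.1 points lie inside that half-width and are not added to it. As a share of variance: (9.1 × 0.20)²/9.5² is about 4%, and (10.3 × 0.40)²/9.5² is about 19%.

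**5. Simulation.** There were 200,000 trials per scenario with 45 per group. Control non-adherence averages 50%, and the intervention multiplies it by 0.4 in each class. A Cochran-Mantel-Haenszel test by entry class stands in for the adjusted analysis.

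| Low-adherence share | Control non-adherence, moderate / low | Gap (points) | Crude power | Adjusted power |
|---|---|---|---|---|
| 50% | 45% / 55% | 10 | 86.6% | 85.8% |
| 30% | 45% / 61.7% | 17 | 86.8% | 86.2% |
| 50% | 40% / 60% | 20 | 86.8% | 86.6% |
| 20% | 45% / 70% | 25 | 86.8% | 86.4% |
| 30% | 40% / 73.3% | 33 | 86.9% | 87.5% |
| 50% | 30% / 70% | 40 | 86.8% | 89.2% |
| 20% | 40% / 90% | 50 | 86.8% | 88.7% |
| 30% | 30% / 96.7% | 67 | 87.0% | 93.3% |

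With no true effect, type I error over all randomisations is 4.5% to 4.6% for the crude test and 4.9% to 5.0% for the adjusted one.

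An imbalance of at least 10 points in low-adherence share occurs in 23% to 34% of trials, and of at least 20 points in 2% to 7%. A 20-point imbalance moves a null RR from 1.00 to about 1.04 to 1.31, or the inverse. Among trials with at least that imbalance, the crude test rejects in about 5% to 23%.

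**The case against.** The strongest reply is that nothing here is an error. Chance imbalance under randomisation is ordinary sampling error, and the crude interval already allows for it. Leaving a 90-patient pragmatic trial unstratified is an accepted choice. An adjusted RR is already planned, and its covariate list may sit in a statistical analysis plan that is not shown. The low-adherence share and the prognostic gap are assumed. Other recorded factors, such as disease activity, type of non-adherence or clinic, might predict as well. The Blinding section also gives the analysis to two blinded researchers, which limits choosing covariates to favour a group.

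Most of this stands, and it rules out three stronger readings that a reader might infer:

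- **That imbalance biases the primary result or inflates false positives.** It does not; overall type I error is about 4.5%.
- **That the plan has no adjustment.** It has one, with unnamed covariates.
- **That the list is known to be unstratified.** The allocation section is silent on strata and blocks, and the flowchart in Appendix 2 is not shown. The imbalance figures hold only if randomisation is simple.

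What the reply does not remove is that the protocol itself names the crude ratio as the measure of efficacy, and that ratio cannot use baseline adherence. Blinded analysts reduce the scope for data-driven covariate choice but do not end it, because nothing requires covariates to be fixed before between-group comparisons are seen.

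**Conclusion.** The point holds as a modest, nearly costless improvement; it does not correct an error. The crude RR discards the baseline adherence information that the trial collects, and the adjusted RR is not tied to it.

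Under the assumed inputs, adjustment gives power of about 86% to 93% against about 87% crude. For gaps of 20 to 40 points the change runs from a loss of 0.4 to a gain of 2.3 percentage points. A gain of about 6 points needs a gap of 67. If entry level is weakly prognostic, nothing is gained and under one point may be lost.

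The other benefit is conditional. Should the groups differ markedly in entry level, a prespecified adjusted estimate is easier to defend than a crude one. The validity of the crude test and the sample size of 90 are not in question.

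**What to change.** In Statistical Analysis, name the Time 0 MGLT YES count, or the class (1–2 against 3–4 YES), as a prespecified covariate in the robust-variance Poisson model. Make that adjusted RR the main estimate, and keep the crude RR with its interval as a supporting result. Fix this before any outcome is seen by group; it can still be done after recruitment has begun.

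The cost is one sentence. It needs no new data and no change to the 90 participants. The downside is that the main RR becomes model-based instead of a simple ratio of incidences. Using the YES count also assumes a form for its relation to outcome, which the two-level class largely avoids.

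Stratifying the list by MGLT class, with blocks, is optional and applies only if allocation has not begun. Power with both changes is 86.4% to 93.7%, little beyond adjustment alone. Blocks also make assignments somewhat more predictable to the unblinded staff who deliver the intervention.

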#### Data Collection

Data collection will be carried out by a team of scientific initiation scholarship holders, duly trained and qualified, under the guidance of the other researchers, including the course of Good Clinical Practices through a web platform (https://gcp.nidatraining.org/). We will use the semi-structured interview technique with questionnaires designed specifically for this study for initial data collection, prior to the proposed intervention program (Appendix 3), and at the end after 6 months of the

intervention program (Appendix 4). Validated instruments for the Brazilian reality will be used, such as the Brasil SF-36[7], which captures the participants' quality of life and the Morisky-Green-Levine Test (MGLT)[8] to measure the degree of non-adherence, as well as the Lichtiger Index[9] to determine the clinical activity of UC. We will also collect secondary data from the participants' medical records, when necessary. A form will be used to record the interventions carried out that will make up the intervention program (Appendix 5). The data will be entered in a database built with the SPSS® statistical package, version 21.0.

#### Blinding

Participants will be identified with a code throughout the study, their names being omitted. The table with names and codes will be available only to those responsible for implementing the interventions (two non-blind researchers). Two other researchers will be responsible for collecting and entering the database in duplicate, to reduce the chances of errors at this stage. Two blind researchers different from the previous ones will do the analysis of the database in duplicate.

#### Intervention Program

Participants in the CG will not receive the interventions, while those in the IG will receive the intervention program individually in a private environment. The intervention program will consist of educational interventions and behavioral interventions, following previously established frequencies, as explained below.

Educational Interventions:

- A video lasting about 5 minutes will be played, presenting basic content about IBD and the importance of adherence to prescribed drug treatment, prepared by the research team according to the script established in Appendix 6 and text in Appendix 7. The video is available at the following link: link: https://youtu.be/vcvm9DXAXNg. This intervention will be carried out at Time 0;
- A printed educational leaflet (Appendix 8) will be delivered, presenting basic contents about UC and the importance of adherence to prescribed drug treatment, prepared by the research team based on available scientific evidence,

according to the script established in Appendix 9. The subject will have 10 minutes for silent reading, and at the end, the team will be available to answer the questions of the participants. This intervention will be carried out at Time 0;

- will be oriented on the drugs prescribed for UC and available for dispensing at FIMAE (Appendix 10) according to the list of clinical protocols[5]. Verbal guidelines will follow the script described in Appendix 11, using as reference the drug monographs available in the Micromedex® database[10]. This intervention will be carried out: at Time 0, or when there is a change in medication during the study period, or when the participant has doubts about medication;

Behavioral Interventions:

- a therapeutic regimen will be prepared according to the model shown in Appendix 12. Participants who demonstrate difficulties in understanding the written guidelines will additionally receive a Pharmaceutical Guidance Table[11] (Anexx A), ), in order to facilitate the understanding of the times and quantities of each prescribed drug. This intervention will be carried out: at Time 0; or when there is a change of medication during the study period; or when the participant has doubts about the therapeutic regimen;
- Short Message Service (SMS) messages will be forwarded to the cell phones registered by the participants:
  - reminder messages of the service date for acquiring medication at FIMAE (Appendix 13). This intervention will be carried out at least 2 days before the return date and 2 hours before the scheduled time;
  - motivational messages with the contents exemplified in Appendix 14. This intervention will be carried out once a week.

